## **19.2 *Exploratory post-randomisation effect modifier analysis***

**Do app usage levels and patterns up to 3-months influence the effect of STEPS on the primary behaviour problems outcome at 3-months and the secondary behaviour problems outcome at 12-months?**

**Does contact within clinical services outside of the service that the child had been referred to up to 3-months influences the effect of STEPS on the primary behaviour problems outcome at 3-months?**

**Does contact within clinical services outside of the service that the child had been referred to up to 12-months influences the effect of STEPS on the behaviour problems secondary outcome effect at 12-months.**

Two exploratory post-randomisation effect modification analyses will be conducted. First, we will analyse the impact of the app usage (likely in terms of number of completed modules or total time spent in the app) collected up to T2 on the effects of STEPS on the primary ODD outcome measured at 3 months post-randomisation (T2) and the secondary ODD outcome measured at 12-months (T5). Second, the impact of clinical contact/care: up to 3 months (T2) on the effects of the STEPS app on the ODD primary outcome at 3 months, and up to 12 months (T5) on the effects of the STEPS app on the ODD secondary outcome at 12 months. Clinical contact/care will include self-initiation of treatment during the trial up to the two specified time points. The clinical care variables used as post-randomisation effect modifier will be extracted from the service use form (the CA-SUS; see section 10.4.1 ‘Resource use data’) and will likely be somewhat post hoc as we are not currently sure which variables are most appropriate; this approach will be made clear to the reader in the publication. We plan to use appropriate causal methods for post-randomisation variables to explore whether the effects of interventions differ by these variables, such as principal stratification analysis (Dunn et al, 2015).

Up to date versions of either the Stata or R software programs will be used for analysis. Further detail of the analyses described in this section will be provided in a statistical analysis plan.

### **19.3 Health economic analysis**

#### **Is STEPS cost- effective compared to WAU over the 3-month and 12-month follow-up periods?**

The economic evaluation will adopt the NHS/personal social services perspective preferred by NICE, but will also include education-based services, given the age of the population. Resource-use data collected using the CA-SUS will be costed using nationally applicable unit costs (e.g., PSSRU Unit Costs of Health and Social Care, NHS Reference Costs, BNF for medications). The STEPS app will be costed in consultation with the system developers.

The primary economic evaluation will be a cost-utility analysis carried out at 3-months post-randomisation with outcomes expressed in terms of quality adjusted life years (QALYs), using the CHU9D proxy completed by a parent. Secondary economic analyses will include: (i) a cost-utility analysis at 12-months post-randomisation to assess cost-effectiveness subsequent to formal assessment and treatment; (ii) a cost-effectiveness analysis undertaken at both 3-months and 12-months using the primary clinical measure of outcome (SNAP-IV ODD score) and (iii) a cost-utility analysis undertaken at both 3-months and 12-months combining QALYs for both the young person (using the CHU9D) and the primary parent/caregiver (using the EQ-5D-5L). Appropriate sensitivity analyses will be carried out, dependent on any assumptions made in relation to the costing of the intervention, the method of measurement of outcomes or the approach to combining QALYs for young people and their primary carer.

Costs and outcomes will be compared at the 3-month and 12-month follow-up points and presented as mean values by trial arm with standard deviations. Mean differences in costs and 95% confidence intervals will be obtained by non-parametric bootstrap regressions to account for the non-normal distribution commonly found in economic data. To provide more relevant treatment-effect estimates, analyses will include adjustment for baseline covariates (Assmann, Pocock, Enos, & Kasten, 2000), which will be pre-specified and in line with the clinical analyses. Cost-effectiveness will be assessed using the net benefit approach following standard approaches (Briggs, Wonderling, & Mooney, 1997). A joint distribution of incremental mean costs and effects for the two groups will be generated using non-parametric bootstrapping to explore the probability that each of the treatments is the optimal choice, subject to a range of possible maximum values (ceiling ratio) that a decision-maker might be willing to pay for an additional QALY (or unit improvement in behaviour problems). Cost-effectiveness acceptability curves will be presented by plotting these probabilities for a range of possible values of the ceiling ratio (Fenwick & Byford, 2005). These curves are a recommended decision-making approach to dealing with the uncertainty that exists around the estimates of expected costs and expected effects associated with the interventions under investigation and uncertainty regarding the maximum cost-effectiveness ratio that a decision-maker would consider acceptable. We will additionally undertake a sensitivity analysis involving the extrapolation of costs and benefits into the future if the trial results suggest this would be worthwhile and the OPTIMA Data Monitoring Committee are in agreement.

## **20. Data monitoring**

### **20.1 Programme Steering Committee**

The Programme Steering Committee (PSC), a body independent of the research team will provide formal oversight and expert advice for the overall OPTIMA programme, which includes an oversight over the present trial. Its role is to ensure that the trial is conducted in a rigorous and timely manner and consider any proposed changes to the agreed programme of research. The PSC consists of an independent chair, statistician, digital health expert, digital mental health interventions expert, two parents of a child with ADHD, and health economics expert. The PSC will meet approximately every six months, with one meeting coinciding with the end of the internal pilot, to provide advice to the funder whether the trial should continue.

### **20.2 Data Monitoring Committee**

The Data Monitoring Committee (DMC) is an independent body of experts that has been established to monitor the quality of trial data and the safety of participants. The DMC will have access to unblinded data if they wish. The DMC will be responsible for monitoring the overall conduct of the study, including recruitment, protocol compliance, accuracy and completeness of data collection. Based on this information, the DMC will make recommendations to the PSC, the Funder and the Sponsor on whether the study should continue or whether there are any ethical or safety reasons why the study should be modified or terminated. Any key changes to the study design and methodology will be reviewed by the DMC. The members of the DMC are completely independent of the trial and consist of an independent chair, statistician, and clinical

The electronic version of this document is the latest version. It is responsibility of the individual to ensure that any paper material is the current version. Printed material is uncontrolled documentation.

expert. The DMC will meet approximately every six months, shortly before a PSC meeting. One of the meetings will coincide with the end of the internal pilot, to determine whether the trial should continue. The DMC and the PSC will be given a charter to outline their tasks and responsibilities.

## 21. Harms

### 21.1 *Specification, Timing and Recording of Safety Parameters*

Please see section 21.2 below for adverse event definitions and reporting parameters. The risk of participants experiencing any adverse events during this trial as a result of using STEPS is very low. Adverse events concerning parental or child physical and mental health will be monitored throughout the trial. Any physical or mental health difficulties spontaneously disclosed by a parent in their communication with researchers will be entered into the Red Pill database using the OPTIMA adverse events form created specifically for the study (see Appendix 4). Moreover, at each timepoint, participants will be asked to complete a formal questionnaire on adverse events (Medical and psychological events and difficulties questionnaire) that happened to them and their child. This information will be collected online using ePRO. The forms will be reviewed regularly, and all adverse events will be recorded on the OPTIMA adverse events form in the Red Pill database. All participants that experience a serious adverse event will be followed-up by the researchers, who have completed Level 2 safeguarding training, until the event is resolved. Where necessary, the participant's clinical service which accepted the referral will be informed about the event.

### 21.2 *Procedures for Recording and Reporting Adverse Events*

#### 21.2.1 Definitions of adverse events.

**Adverse Event (AE):** Any untoward medical occurrence in a subject to whom a therapy has been administered including occurrences which are not necessarily caused by or related to that therapy.

**Adverse Reaction (AR):** Any untoward and unintended response in a subject to a therapy which is related to any duration of therapy administered to that subject.

**Unexpected Adverse Reaction (UAR):** An adverse reaction the nature and severity of which is not consistent with the information known about the therapy in question in the view of the investigator

**Suspected Unexpected Serious Adverse Reactions (SUSAR):** Any serious adverse events that is deemed to be related to the trial intervention and unexpected (not listed in the protocol as an expected side effect of the intervention).

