### **10.3.9 Adverse events**

*T1, T2, T3, T4, T5, safety outcome.*

This will be measured with the Medical and psychological events and difficulties questionnaire (MAPED), which has been developed for the study (see Appendix 3). Parents will be asked to report retrospectively any physical and/or mental health difficulties they or their child have experienced in the last three months. They will also be asked to report any difficulties they or their child have had with daily activities. These will be used to monitor safety and to provide descriptive information about adverse events experienced during the trial.

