## 11. Process Evaluation

The process evaluation will follow the Medical Research Council guidelines for evaluating the implementation of complex interventions (Moore et al., 2015) and will be described in more detail in a separate protocol. Briefly, the process evaluation will use baseline and post-intervention quantitative trial data (e.g., app usage data, including counts and time) and qualitative data from semi-structured interviews with parents and clinicians (e.g., expectations, perceptions of impact, barriers to engagement) and textbox responses to open questions to explore the mechanisms for intervention implementation and impact.

All parents will be invited to respond to questions about: (1) their expectations of the trial (baseline) and (2) accounts of their experience of parenting during trial participation (T2 through to T5), see '10.3 Other measures'. This information will be collected using Red Pill online data collection platform. Detailed data on usage of the app will be automatically recorded for each participant in the STEPS arm. For details, see '10.3 Other measures'. Post-intervention, researchers will conduct remote (telephone, video call or email) in-depth, semi-structured interviews with a subgroup of parents in the intervention group (n ~ 50). Maximum variation, purposive sampling will be used to ensure that a full range of views and experiences are captured (taking account of demographic factors and levels of app engagement). In addition, telephone interviews

The electronic version of this document is the latest version. It is responsibility of the individual to ensure that any paper material is the current version. Printed material is uncontrolled documentation.

with clinicians (n ~ 10) will explore perceptions of the app and its perceived impact on preparing families for the formal clinical assessment. The interview schedules will be developed with Patient and Public Involvement (PPI) panel input. Interview data will be audio recorded and analysed using thematic analysis (Braun & Clarke, 2013), applying a framework approach (Gale et al 2013). As a thank you for taking part, all parents taking part in qualitative interviews will receive a £20 shopping voucher. There will be no incentives for clinicians.

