**In non-CTIMPs, a serious adverse event (SAE) is defined as an untoward occurrence that:**

- (a) results in death;
- (b) is life-threatening;
- (c) requires hospitalisation or prolongation of existing hospitalisation;
- (d) results in persistent or significant disability or incapacity;
- (e) consists of a congenital anomaly or birth defect; or
- (f) is otherwise considered medically significant by the investigator.

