### Adverse Events Form

### Adverse Events Form

This form was completed based on:

1. A report from a research assistant?
2. A completion of an online questionnaire?

| 1. Details of adverse event
(describe below what has been reported)

[free text up to 500 characters] | 2. Medical/physical health
1. Cardiovascular
2. Respiratory
3. Hepatic
4. Gastro-intestinal
5. Genito-urinary/renal
6. Endocrine
7. Haematological
8. Musculo-skeletal
9. Neoplasia
10. Neurological
11. Psychological
12. Immunological
13. Dermatological
14. Allergies
15. Eyes, ear, nose, throat | 3. Mental health/behaviour

0. No
1. Yes | 4. Relationships or daily activities difficulties

0. No
1. Yes | 5. Start date | 6. Outcome
1. Resolved
2. Resolved with treatment/intervention
3. Ongoing | 7. End date | 8. Relationship to intervention
1. Definitely related
2. Likely
3. Possibly
4. Unlikely
5. Not related | 9. Expected?
1. Expected
2. Unexpected | 10. Is this event serious?
0. No
1. Results in death
2. Is life-threatening
3. Requires hospitalisation or prolongation of existing hospitalisation
4. Persistent or significant disability or incapacity
5. Consists of a congenital anomaly or birth defect | 11. SUSAR?
0. No
1. Yes | 12. Who is involved?
1. Target child
2. Target parent | 13. Has the event led to the family no longer participating in the study?
0. No
1. Yes |

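### The adverse event definition excludes wait-as-usual families and most of the listed expected events, and STEPS-only interviews add an unequal route for spontaneous reports

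*Protocol*

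**What the plan says.** Section 21.2.1 defines an adverse event as "Any untoward medical occurrence in a subject to whom a therapy has been administered including occurrences" not caused by or related to that therapy. The next definition in section 21.2.1 is wider: "a serious adverse event (SAE) is defined as an untoward occurrence that" meets one of six seriousness criteria, with no requirement that a therapy was given or that the occurrence was medical.

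There are two collection routes. The solicited route is MAPED, the study's own questionnaire: "at each timepoint, participants will be asked to complete a formal questionnaire on adverse events" (section 21.1). Its content is broad: "Parents will be asked to report retrospectively any physical and/or mental health difficulties they or their child have experienced in the last three months" (section 10.3.9). After review of the forms, "all adverse events will be recorded on the OPTIMA adverse events form in the Red Pill database" (section 21.1).

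The spontaneous route is also in section 21.1: "Any physical or mental health difficulties spontaneously disclosed by a parent in their communication with researchers will be entered into the Red Pill database", on the same form. Section 11 plans "semi-structured interviews with a subgroup of parents in the intervention group (n ~ 50") after the intervention. Section 16 says that research assistants conduct these interviews.

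The Appendix 4 form opens with a source item, "This form was completed based on", which has two options: a research assistant's report or an online questionnaire.

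**The concern.** The definition does not fit the design. Section 9.4 gives STEPS to WAU families only once their 12-month follow-up is complete, so during the trial they are not subjects who have been given a therapy. The app is used by the parent, so the child is not such a subject in either arm. Yet MAPED asks about parent and child in both arms, and the Appendix 4 form has a code for the target child.

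The spontaneous route is open to both arms, but the STEPS arm has one documented type of researcher contact that WAU lacks.

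Both features point towards an apparent excess of adverse events on STEPS. Adverse events are a safety outcome (section 10.3.9), the expected ones go into the main publication (section 21.3), and the data monitoring committee may see unblinded data (section 20.2). A descriptive by-arm table can mislead without any formal test.

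**Working it through.** **Step 1. Definition against the rest of the protocol**

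| Place | Therapy required? | Medical only? | Who is covered |
|---|---|---|---|
| 21.2.1, adverse event | Yes | Yes | Subject given a therapy |
| 21.2.1, serious adverse event | No | No | Not restricted |
| 10.3.9 and Appendix 3, MAPED | No | No: physical, mental, behavioural, relationships, daily activities | Parent and child, both arms |
| 21.3, expected events | No | No | Child, sibling, family, parent |
| Appendix 4 form | No | No | Target child or target parent |

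Read literally, a WAU family can have a serious adverse event but not an adverse event.

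**Step 2. Expected events that fall outside the definition.** Section 21.3 lists 2 school or community items, 5 family items and 4 parent wellbeing items, 11 in all. The 2 + 5 = 7 school and family items are mainly behavioural or social, or concern people who do not use the app. So 7 of 11 fall outside even in the STEPS arm. The 4 parent items fit only if mood, stress, fatigue and sleep count as medical, and then only for STEPS parents.

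**Step 3. Does equal questionnaire collection settle it?** Not fully. Section 21.1 sends the reader to section 21.2 for the definitions and then says that adverse events found on review are recorded. MAPED answers arrive equally from both arms, but the definition decides which of them count. Staff must either disregard it or leave out WAU events.

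**Step 4. Extra contact in the STEPS arm.** Section 13 gives 176 per arm. This reproduces: 2 × (1.960 + 1.282)² / 0.4² = 131.4, rounded up to 132, and 132 / 0.75 = 176.
- Interviews as a share of those randomised to STEPS: 50 / 176 = 28.4%.
- As a share of those expected to be retained: 50 / 132 = 37.9%.
- The planned number of WAU interviews is 0.

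**Step 5. Illustration only.** The documents give no rate at which interviews would reveal a difficulty not otherwise recorded. Call it p, an assumption. Extra STEPS parents with a report = 50 × p, and the shift in percentage points = 100 × 50 × p / 176.

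| p (assumed) | Extra parents | Shift, points of 176 |
|---|---|---|
| 5% | 2.5 | 1.4 |
| 10% | 5 | 2.8 |
| 30% | 15 | 8.5 |
| 50% | 25 | 14.2 |

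These shifts arise with no true difference between arms, but only if all sources are pooled.

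**Step 6. Can the sources be separated afterwards?** Only in part. Section 17 lets participants complete questionnaires or give adverse event information by phone to a research assistant. A MAPED answer taken by phone and a disclosure in an interview could both be coded as a research assistant's report.

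**The case against.** The case on the other side is substantial. The main route is the same in both arms: MAPED is scheduled at T1 to T5 for everyone, and section 16 promises equal prompts to complete measures. With three-month recall at roughly three-monthly follow-ups, it would also pick up many of the events mentioned at interview. The spontaneous route covers any parent, and WAU parents do speak to researchers, through follow-up calls and the online drawing task (section 17). The adverse event sentence is generic wording, and nothing tells staff to discard WAU events. No between-arm test of harms is stated, there are no formal statistical stopping rules (section 21.4), and table layout is usually left to the analysis plan.

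Most of this stands, and it rules out three stronger readings that a reader might draw:
- That adverse events as a whole are collected unequally, or that spontaneous reports come only from STEPS contacts. Sections 21.1 and 16 say otherwise.
- That technical support is a further unequal route. Section 9.1.2 says only that it exists, and section 17 mentions external staff for app support, so it is not shown to be communication with researchers.
- That the WAU count will be zero. That follows from the literal wording, not from any operating instruction.

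The objection does not remove two things. The definition contradicts the text around it, and a definition is protocol content. The interviews are a researcher contact with no WAU counterpart, feeding a form whose source item cannot isolate them.

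**Conclusion.** The definition in section 21.2.1 conflicts with the protocol's own collection rules, its serious adverse event definition and its list of expected events, and should be reconciled with them. That conclusion rests on the wording alone.

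The interviews create an avoidable ascertainment imbalance: up to about 28% of the STEPS arm has an extra occasion to disclose, against none in WAU. Its effect on by-arm counts is unknown. The 1.4 to 14.2 points above rest wholly on assumed yields of 5% to 50%, on events that MAPED missed and on pooled sources, and the protocol does not say that sources will be pooled. A reader might infer that the comparison of harms is biased. The documents support only that pooled counts may tilt towards an excess on STEPS. The point merits a change because the remedy is cheap.

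**What to change.** 1. Section 21.2.1: define an adverse event as any untoward occurrence (medical, psychological, behavioural or social) in the index parent or child, in either arm, from randomisation to T5, whether or not related to STEPS. State where the sibling item in section 21.3 belongs, because the form codes only target child and target parent.
2. Appendix 4: add an interview source code, distinct from MAPED answers given by phone.
3. Base by-arm adverse event summaries on MAPED-elicited events. List spontaneous and interview disclosures separately. Serious events from any source are still reported.

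The cost is one definition, one source code and one split table. The downside is that the main by-arm summary leaves out spontaneous reports, although they are still listed.

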**In non-CTIMPs, a serious adverse event (SAE) is defined as an untoward occurrence that:**

- (a) results in death;
- (b) is life-threatening;
- (c) requires hospitalisation or prolongation of existing hospitalisation;
- (d) results in persistent or significant disability or incapacity;
- (e) consists of a congenital anomaly or birth defect; or
- (f) is otherwise considered medically significant by the investigator.

#### 21.2.2 Adverse events reporting parameters

**An SAE occurring to a research participant should be reported to the main REC, where in the opinion of the Chief Investigator (CI) the event was:**

- Related – that is, it resulted from administration of any of the research procedures, and
- Unexpected – that is, the type of event is not listed in the protocol as an expected occurrence.

All SAEs, SARs and SUSARs (excepting those specified in this protocol as not requiring reporting) should be reported immediately to the Chief Investigator and to the Sponsor.

Reports of Serious Adverse Events (SAEs) that are **related** to the study (i.e., they resulted from administration of any of the research procedures) and **unexpected** (i.e., not listed in the protocol as an expected occurrence) should be submitted to the REC using the [Non-CTIMP safety report to REC form](#).

These should be sent within 15 days of the Chief Investigator becoming aware of the event. Reports of SAEs in double-blind trials should be unblinded. There is no requirement for annual safety reports in addition to the information provided through the annual [progress report](#). More detailed description of adverse events reporting parameters is included in Table 3.

Table 3. Adverse events reporting parameters.

|                                                                        | Who                | When                                                                                                                           | How                                                                                                                                                                                                                        | To Whom                                                                                                             |
|------------------------------------------------------------------------|--------------------|--------------------------------------------------------------------------------------------------------------------------------|----------------------------------------------------------------------------------------------------------------------------------------------------------------------------------------------------------------------------|---------------------------------------------------------------------------------------------------------------------|
| SAE                                                             | Chief Investigator | Within 15 days of CI becoming aware of the event                                                                               | SAE Report form for Non-CTIMPs, available from NRES website.                                                                                                                                                               | Main REC with a copy to the sponsor                                                                                 |
| Urgent Safety Measures                                          | Chief Investigator | Immediately

Within 3 days                                                                                               | By phone

Notice in writing setting out reasons for the urgent safety measures and the plan for future action.                                                                                                       | Main REC

Main REC with a copy sent to the sponsor. The MREC will acknowledge this within 30 days of receipt. |
| Progress Reports                                                | Chief Investigator | Annually (starting 12 months after the date of favourable opinion)                                                             | Annual Progress Report Form (non-CTIMPs) available from the NRES website                                                                                                                                                   | Main REC with a copy to the sponsor                                                                                 |
| Declaration of the conclusion or early termination of the study | Chief Investigator | Within 90 days (conclusion)
Within 15 days (early termination)
The end of study should be defined in the protocol | End of Study Declaration form available from the NRES website                                                                                                                                                              | Main REC with a copy to the sponsor                                                                                 |
| Summary of final Report                                         | Chief Investigator | Within one year of conclusion of the Research                                                                                  | No Standard Format
However, the following Information should be included:
Where the study has met its objectives, the main findings and arrangements for publication or dissemination including feedback to subjects | Main REC with a copy to be sent to the sponsor                                                                      |

All completed adverse event questionnaires will be reviewed by the research team to identify any Suspected Unexpected Serious Adverse Reactions (SUSAR). If an event meets the definition of a SUSAR (see box below) then the member of staff to whom the event was disclosed must inform Chief Investigator within 24 hours of becoming aware of the serious adverse event and provide all necessary information. Each case will be assessed by the Chief Investigator and team clinical expert for seriousness, expectedness and relatedness to the study. The CI will then take appropriate action, which may include halting the study and informing the Sponsor of such action. If the event is deemed serious, unexpected and related to the study intervention they shall inform the REC using the reporting form found on the HRA web page within 15 days of knowledge of the event, and include the co-Sponsors (King's College London and The South London and Maudsley NHS Foundation Trust) in all communications. They shall, within a further eight days send any follow-up information and reports to the REC and make any amendments as required to the study protocol and inform the REC as required.

All SUSARs will be recorded and closely monitored by the research team until resolution, stabilisation, or until it has been shown that the study intervention is not the cause.

The electronic version of this document is the latest version. It is responsibility of the individual to ensure that any paper material is the current version. Printed material is uncontrolled documentation.

Any participant who experiences a SUSAR may be withdrawn from the study at the discretion of the CI and the Sponsor. Every withdrawal will be examined by the DMC. The DMC will be made aware of all serious adverse reactions/SUSARs at their regular meetings.

The CI will have responsibility for informing the other sites of the SUSAR and any relevant safety information, which may be delegated to the Trial Manager. The CI will also inform the local clinical care team (CAMHS or Community Paediatrics) or GP under which the participant is routinely seen for of any SUSARs (details of which are obtained at screening/referral).

Events categorised in the protocol as an expected (see 20.3), do not need to be reported.

